##### Pre- and post-stroke sleep history and sleep questionnaires

Pre-stroke sleep history: at days 1 to 4 following stroke, patients are shortly interviewed about pre-stroke sleep problems. Interview questions include (1) questions about usual bedtime, sleep latency, rise time and sleep duration during the week and on the weekends within the last month before stroke, (2) bed- and rise time and sleep duration during the two nights before stroke, (3) daytime naps the 2 days before stroke and (4) any previous significant sleep disturbances within the last month before stroke and intake of medication.Post-stroke sleep history is assessed at visit 6 and 7 and include (1) questions about usual bedtime, sleep latency, rise time and sleep duration during the week and at the weekends within the last month from now and (2) occurrence of any significant sleep disturbances within the last month and intake of medication.Sleep and depression questionnaires: all stroke patients fill in the following questionnaires to measure sleepiness/fatigue, likelihood for sleep apnoea and symptoms of depression at visits 1, 6 and 7:
Epworth Sleepiness Scale (ESS) [35].Fatigue Severity Scale (FSS) [36]Berlin Questionnaire for Sleep Apnoea (BQSA) [37]Beck Depression Inventory (BDI-II) (validated German translation of [38])

Data collection of primary and secondary outcome measurements continues even if a patient of the ASV+ group discontinues ASV treatment. The only condition when data collection stops is if patients withdraw their informed consent. Data collected until this point in time will be kept and analysed as agreed by patients signing the informed consent forms.

### Data management and study monitoring

The case report forms (CRFs) in this trial are implemented electronically using a dedicated electronic data capturing (EDC) system (REDCap). The EDC system was activated for the trial only after successfully passing a formal test procedure. All data entered in the electronic CRFs are stored on a Linux server in a dedicated mySQL database.

Study monitoring including source data verification of a selected subject at each centre is performed by the Clinical Trial Unit (CTU) of the University of Bern, Switzerland. With the informed consent, patients agree that relevant data can be viewed and shared with the research team that initiated the study (coordinating research team in Bern), with the ethical and regulatory authorities (including the representative of the trial’s insurance in case of a potential study-related damage) and the trial’s monitors.

### Statistical analysis

Descriptive summary statistics for efficacy and safety variables will be presented for the entire population and by study arm (no SDB patients, and SDB patients randomized to the ASV+ and ASV- arms). Inferential statistical methods will be used to highlight interesting aspects of the data and primarily for the comparison of outcome variables in the two randomized arms. In addition, comparisons of selected outcomes will be carried out between the two cohorts. The significance level of all statistical tests will be 5% and no control for multiplicity will be applied. Corresponding 95% confidence intervals will be presented as appropriate.

Two main analysis populations will be used:
*Full Analysis Set (FAS)*: this population will include all enrolled patients. In line with the intent-to-treat principle, randomized patients will be analysed according to the treatment group assigned at randomization. The FAS will be the main analysis population for efficacy and safety variables. In particular, it will be the primary population for the comparative analysis of the two randomized treatment groups.*Per-protocol (PP) population*: it will include randomized patients fulfilling all selection criteria and sufficiently compliant with the protocol. The list of criteria, leading to exclusion from the PP analysis, which, among other criteria, will consider the compliance with ASV procedures, will be finalized before database closure for the primary analysis.

The comparative analysis of infarct volume data will be performed using an analysis of covariance model with adjustments at least for the stratification variables used at randomization. In case of violation of the statistical validity conditions for the model, a suitable non-parametric alternative model will be employed, such as the Van Elteren test.

Between-arm comparisons of continuous variables will be performed using the same methodology as for the primary variable, whereas models may include additional explanatory variables, such as the baseline value of specific outcome variables assessed at study end. Logistic regression will be used for comparisons based on binary variables.

Furthermore, similar models will be used to compare outcome variables between patients from the two cohorts of randomized patients and no SDB patients. Due to the non-randomized design and the definition of the cohorts, the set of explanatory variables included in these models will be different: AHI will not be included, but other potential confounders, such as age and gender may be. No interim analysis of efficacy endpoints is planned. Primary and secondary efficacy outcomes will be analysed after all randomized patients have completed the study or have left it prematurely. Interim analyses of safety may be performed. The analysis of safety data will use descriptive statistical methods. Deviations from the analyses outlined in this section and in the statistical analysis plan will be listed and justified in the Clinical Study Report. No imputation of missing variables will be employed in the primary comparative analysis of efficacy parameters in the two randomization groups. For supportive analyses, imputation strategies considered conservative may be used.

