### Intervention: adaptive servo-ventilation

The investigational device for ASV in this trial is the “AirCurve™10 CS PACEWAVE” device, (ResMed Ltd., [name]). It is indicated and approved for clinical use in Switzerland, European Union, and other countries. For this trial, the device is strictly applied in accordance to its approved indications and the instruction manual. Commercially available and approved full-face or nasal masks are used as patient–ventilator–interface to achieve optimal mask fit without relevant leakage. As in clinical routine, all patients will undergo education and training in the use of the device.

In case of an acute upper respiratory tract infection, the intervention will be temporarily or constantly discontinued based on the study physicians and pulmonary physicians’ decision. ASV treatment will be stopped if a patient reports unusual chest pain, severe headache, increased breathlessness or in case of new evidence for congestive heart failure (as defined in the exclusion criteria Table 1) and on patients’ request.

No comparator or sham treatment is administered. SDB patients not randomized to ASV will be treated according to best current medical practice. We decided against sham ventilation due to the following reasons: (1) Sham ventilation may cause even greater distress in patients than effective ventilation and patients will not perceive any benefit in terms of an increase in sleep quality and an improvement in daytime sleepiness. This may lead to a greater decrease in treatment compliance in sham versus effectively treated patients. (2) As described by Tomfohr and colleagues [26], stroke patients’ burden of a ventilation intervention is already high and informing them that they may be randomized to a placebo ventilation will further decrease the number of given informed consents. (3) The use of a subtherapeutic ventilation pressure may act as a partial treatment of nightly occurring apnoeas and hypopnoeas and thus decrease discriminatory power when comparing the two randomized groups.

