
##### Assessment of ASV treatment compliance

Compliance to ASV treatment is checked daily during the initiation of ASV treatment using the devices internal recordings. Thereafter, verification of compliance takes place at clinical controls at visits 2, 4, 5 and 6. Sufficient compliance is defined as a cumulative ASV use in ≥ 70% of all nights and ≥ 4 h per night in the first 3 months after stroke. All patients who started ASV treatment/training will be analysed as ASV patients (intention to treat; ITT). For secondary analyses, patients with SDB are stratified according to their compliance: compliant patients (per protocol, PP) will be compared to non-compliant participants and to participants who did not receive ASV-treatment.

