### Safety

Serious adverse events (SAE), serious adverse device effects (SADE) and serious adverse incidents (SAI) are assessed at each centre and reported to the centres’ local ethical committees according to their requirements and within 24 h of awareness to the coordinating centre in Bern.

The coordinating centre in Bern also submits an annual safety report to their ethical committees and to centres’ principal investigators (PI). All PIs are responsible to continuously evaluate the risk-benefit profile of the intervention for each examined patient. Findings or available data indicating an imbalanced risk-benefit profile must be reported to the ethical authorities and the PIs must take the necessary steps.

In case of a SAI, each centre will contact the responsible person for medical device vigilance in order to decide whether reporting to the national health surveillance authorities according to the legal requirements at each centre is indicated.

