## Discussion

eSATIS trial is the first trial to assess the impact of immediate treatment of significant SDB (AHI > 20/h) in acute ischaemic stroke patients with non-invasive ASV on infarct progression in a prospective interventional randomized controlled design. The trial will give information on the feasibility and efficacy of ASV treatment in patients with stroke and SDB and allow assessing the impact of SDB on stroke outcome. Diagnosing and treating SDB during the acute phase of stroke is not yet current medical practice. Evidence in favour of ASV treatment from a randomized multicentre trial may lead to a change in stroke care and to improved outcomes.

Limitations of this trial include the following: (1) The compliance to ASV is expected to be around 50%. This will have an impact on the interpretation of results. (2) The treatment is open label, which may result in a bias affecting the assessment of secondary clinical outcomes. However, sham ventilation may cause even greater distress in patients than effective ASV treatment without beneficial effects on sleep quality and improvement of daytime sleepiness and is ethically questionable. (3) It is unknown whether the sample size of 134 randomized patients will be sufficient to detect the real treatment effect, since no data on the impact of ASV treatment on the evolution of the lesion volume are available so far.

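### Neither named analysis set gives ASV harm per exposed patient: the assigned-arm FAS dilutes it, the per-protocol set tends to select it out, and two sections disagree on who counts as an ASV patient

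*Protocol article*

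**What the plan says.** Four parts of the protocol article bear on this.

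- **Statistical analysis.** Two main populations are named. Of the FAS the article says "this population will include all enrolled patients", that "randomized patients will be analysed according to the treatment group assigned at randomization", and that "The FAS will be the main analysis population for efficacy and safety variables". Of the per-protocol set it says "it will include randomized patients fulfilling all selection criteria and sufficiently compliant with the protocol". Its exclusion criteria will consider compliance with ASV procedures and are to be finalized before database closure. Safety data are analysed descriptively.
- **Assessment of ASV treatment compliance.** "All patients who started ASV treatment/training will be analysed as ASV patients (intention to treat; ITT"). Sufficient compliance means use in at least 70% of nights and at least 4 h per night over the first 3 months, read from the device's internal recordings.
- **Discussion, limitations.** "The compliance to ASV is expected to be around 50" per cent.
- **Intervention and Safety.** "ASV treatment will be stopped if a patient reports unusual chest pain, severe headache, increased breathlessness", and also on new evidence of congestive heart failure or at the patient's request. The Safety section says "Serious adverse events (SAE), serious adverse device effects (SADE) and serious adverse incidents (SAI) are assessed at each centre" and describes how they are reported.

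**The concern.** Analysis by assigned arm protects the randomized comparison, and for efficacy its attenuation is usually conservative. For harm it works the other way: patients in the ASV+ arm with little or no exposure pull the observed rate of device-related events towards the control rate. With compliance expected at about half, this deserves attention.

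The per-protocol set does not repair it. A patient who stops ASV early because of a symptom is likely to miss the compliance threshold, and so to leave the set in which users are examined. Harm is then diluted in one population and selected out of the other.

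The two descriptions of intention to treat also give different ASV groups, so a reader cannot tell which denominator a safety percentage would use. The Discussion says that a favourable result may change stroke care. A patient or clinician weighing ASV would then want the risk among those who actually use it.

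**Working it through.** **The plan's own figure.** The article gives no safety figure. Its sample size fixes the denominator: about 134 randomized 1:1 is 134 / 2 = 67 per arm. The stated power of at least 80% for d = 0.49 (two-sided 5% t test) reproduces: noncentral t gives 0.804 with 67 per arm. This point does not depend on that figure.

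**Step 1: who is an ASV patient?**

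| Patient | By assignment (Statistical analysis) | By start of treatment/training (ASV compliance section) |
|---|---|---|
| Assigned ASV+, never starts | ASV | not covered as ASV |
| Assigned ASV−, starts ASV | not ASV | ASV |
| Assigned ASV+, training only | ASV | ASV, though possibly with no night of use |

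The rules differ in the first two rows. In the third, even the start-based rule does not guarantee exposure.

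**Step 2: what does the per-protocol set keep?** The screening section places treatment between the 2nd and 89th night, which is 89 − 2 + 1 = 88 nights. The threshold is 0.70 × 88 = 61.6, so 62 nights. If the two-week washout under Sleep assessment is taken out, 88 − 14 = 74 nights and 0.70 × 74 = 51.8, so 52 nights. Either way, a patient who stops for good in roughly the first seven weeks cannot be sufficiently compliant, whatever the reason for stopping. Since the exclusion criteria will consider ASV compliance, such a patient would be expected to leave the per-protocol set.

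**Step 3: dilution in the FAS.** Let u be the share of the ASV+ arm that is exposed, and let unexposed patients carry the control risk. Then

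assigned-arm excess risk = u × excess risk in users.

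The article gives neither u nor any event rate, so the following is illustration only. With control risk 5%, risk in users 20% (true excess 15 points) and 67 per arm, control has 67 × 0.05 = 3.4 expected events:

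| u | Assigned-arm excess (points) | Expected ASV+ events |
|---|---|---|
| 1.0 | 15.0 | 13.4 |
| 0.9 | 13.5 | 12.4 |
| 0.8 | 12.0 | 11.4 |
| 0.7 | 10.5 | 10.4 |
| 0.5 | 7.5 | 8.4 |

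The row u = 0.5 would need every non-compliant patient to be wholly unexposed. The compliance definition does not support that.

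**Step 4: what zero events would show.** The one-sided 95% upper bound is 1 − 0.05^(1/n). If 0%, 10%, 20% or 30% of 67 never use the device (assumed), then n = 67, 60, 54 or 47 are exposed:

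- n = 67: 4.4%
- n = 60: 4.9%
- n = 54: 5.4%
- n = 47: 6.2%

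**The case against.** Much can be said for the plan. Comparing safety by assigned arm is defensible and keeps the randomized contrast. Calling the FAS the main population does not bar a supplementary one. Exposure is not ignored: there is a per-protocol set, and secondary analyses compare compliant patients with non-compliant ones and with those who received no ASV. An additional safety set is often left to the analysis plan, which is not shown, and safety is descriptive with no margin, so moving a bound by a point or two overturns no stated conclusion.

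This limits the weight of the point but does not remove it. What the article does fix is an assigned-arm main safety population, a compliance-dependent alternative, and two definitions of the ASV group that disagree. The non-compliant stratum does hold the early stoppers, but it may mix them with patients who were never exposed.

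Three stronger readings are tempting, and the document does not support them:

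- **That half the ASV+ arm never uses the device.** The 50% concerns a threshold of nights and hours. A patient using ASV on 60% of nights is non-compliant but heavily exposed.
- **That only serious events are collected.** The Safety section names serious categories and their reporting routes. It does not say that non-serious events go unrecorded, and the case report form and full protocol are not shown.
- **That the symptoms which stop ASV never reach the safety results.** Those meeting seriousness criteria would be SAEs or SADEs, and unplanned heart-failure hospitalization is part of the clinical composite assessed at visits 4, 6 and 7.

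**Conclusion.** The concern holds in this limited form. As written, the article's main safety population counts little-exposed or unexposed ASV+ patients as exposed, its other main set would tend to exclude patients who stopped early, and its two accounts of the analysed ASV group conflict. Neither set gives harm per exposed patient.

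The size is not derivable from the document. Under an assumed never-user share of 10% to 30%, the assigned-arm excess loses the same 10% to 30%, and the zero-event bound would be 4.9% to 6.2% where the full arm gives 4.4%. Both results assume that unexposed patients carry no device risk. Partial use also dilutes the signal, by an amount that the article does not allow one to calculate. The efficacy comparison and its power are unaffected.

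**What to change.** 1. Reconcile the Statistical analysis and ASV compliance sections, so that one rule states who is analysed as an ASV patient and the intention-to-treat label is attached to assignment only.
2. Keep the FAS safety comparison by assigned arm as it is.
3. Add a descriptive ASV-exposed safety set: at least one night of device-recorded use, whatever the assigned arm. Report events per patient and per nights of recorded use.
4. Tabulate ASV interruptions and stops by recorded reason where available, without presuming that the device caused the symptom. Chest pain or headache after acute stroke can have other causes. The rules for stopping treatment are not touched.

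The exposed set can be fixed together with the per-protocol criteria, which are still to be finalized before database closure. The cost is one or two descriptive tables from device recordings that the trial already checks for compliance. Sample size and power do not change. There are two limits. The exposed set is not a randomized comparison, so it stands beside the FAS table and does not replace it. And with recruitment expected to end in July 2021, about six months after publication, stop reasons not already recorded may be unrecoverable for many patients.

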### Assessment of outcomes

#### Primary outcome: final infarct change from visit 1 to visit 6 on magnetic resonance imaging (MRI)

The infarct volumes (measured in cm^3^) are assessed at visit 1 and visit 6 (see Table 2 displaying which assessments are performed at which visits, according to [27]). We measure infarct volume on DWI (diffusion weighted imaging) MRI scans at visit 1, i.e. after potential lysis therapy and before ASV-treatment, and on T2w MRI scans at visit 6 (see Fig. 2 for illustration). Two independent raters blinded regarding patients’ treatment allocation and presence of SDB assess the primary MRI outcome supervised by two senior neuroradiologists. Change of lesion volume from visit 1 to visit 6 is compared between the treatment groups (SDB ASV+ and SDB ASV−). Change of lesion volume from visit 1 to visit 6 will also be compared between the patient groups with sleep-disordered breathing (SDB ASV+ and ASV− together) and without sleep-disordered breathing (noSDB).

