### Power calculation and sample size

Based on feasibility considerations, approximately 134 patients are expected to be randomized in a 1:1 proportion into the group with ASV treatment and without ASV treatment (SDB ASV+ and SDB ASV-). Based on a two-sided *t* test at the 5% significance level, this sample size will provide at least 80% power to detect an effect size (Cohen’s d) of 0.49 for the between-group difference in primary outcome (difference in infarct size from visit 1 (day 1) to visit 6 (day 90)). Based on preliminary investigations in a similar patient pool, the standard deviation is assumed to be 20 cm^3^ (unpublished data), so that the detectable effect size corresponds to a between-arm difference of approximately 10 cm^3^. In secondary analyses, the outcomes will be compared in patients with and without SDB: the detectable difference is expected to be approximately 10 cm^3^ also for this analysis. Calculations were performed using the statistical software package R (https://www.r-project.org/) [39]. These differences are considered meaningful from a clinical point of view.

Based on these considerations, the planned sample size is considered adequate to address the main study objective.

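### The primary ANCOVA of lesion-volume change does not require or prespecify visit 1 infarct volume as a covariate; naming it would be a free gain in precision of unknown size.

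*Protocol article*

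**What the plan says.** The primary endpoint is a change score in cm³, from DWI volume at visit 1 to T2w volume at visit 6: "Change of lesion volume from visit 1 to visit 6 is compared between the treatment groups" (Primary outcome). The same section places the visit 1 scan after any lysis and before ASV.

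Statistical analysis specifies an "analysis of covariance model with adjustments at least for the stratification variables used at randomization". Randomization gives the stratification variables as study centre and baseline AHI (below 45/h, or 45/h and above). Lesion size is not among them.

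The following paragraph of Statistical analysis turns to the other continuous variables. It applies the same method to them and adds, as a contrast, that "models may include additional explanatory variables, such as the baseline value of specific outcome variables assessed at study end". This is the section's only mention of baseline values as covariates. If the ANCOVA conditions fail, the named example of a fallback is the Van Elteren test.

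The sample size rests on an unadjusted comparison, a two-sided t test with α = 0.05. Power calculation and sample size claims that "this sample size will provide at least 80% power to detect an effect size (Cohen’s d) of 0.49".

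**The concern.** An absolute change in volume can depend on the starting volume. Table 1 excludes lesions below 1.5 cm in diameter and states no upper size limit, so starting volumes may vary widely. A sphere of 1.5 cm diameter has a volume of π/6 × 1.5³ = 1.77 cm³. Such a lesion cannot shrink by the 10 cm³ that the trial is sized to detect between arms, whereas a large infarct can.

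A plan followed exactly as written could therefore analyse the change score without the pre-treatment volume. If that volume predicts the change, two things are given up:

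- **Precision.** Variance that the model could explain stays in the error term. The sample size was set by feasibility, and the Discussion says it is unknown whether 134 patients will be enough.
- **Prespecification.** A minimum covariate set that is open above leaves it undecided in this document whether the primary estimate is adjusted for baseline.

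**Working it through.** **Inputs from the Protocol article (Power calculation and sample size).** Two-sided α = 0.05; 134 patients randomised 1:1, so 67 per arm; d = 0.49; SD 20 cm³. I read this as the SD of the volume change, because d is stated for the change. The target difference is then 0.49 × 20 = 9.8 cm³, which the text rounds to 10.

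**Step 1: reproduce the stated power.** For an exact two-sample t test, df = 132 and noncentrality = 0.49 × √(67/2) = 2.84. Power is 80.4%, and 67 per arm is the smallest size that reaches 80%. The difference detectable with exactly 80% power is 9.75 cm³. The stated figure holds.

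**Step 2: add visit 1 volume as a covariate.** Let r be the correlation between visit 1 volume and volume change. The document does not give it, so the values below are assumptions.

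- Residual SD = 20 × √(1 − r²), with one further df lost (131).
- N giving the precision of 134 unadjusted patients = 134 × (1 − r²).

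| absolute r | residual SD (cm³) | power at 9.8 cm³ | detectable at 80% (cm³) | equivalent N |
|---|---|---|---|---|
| 0 | 20.0 | 80.4% | 9.75 | 134 |
| 0.2 | 19.6 | 81.9% | 9.56 | 129 |
| 0.3 | 19.1 | 83.9% | 9.30 | 122 |
| 0.5 | 17.3 | 90.2% | 8.45 | 101 |
| 0.6 | 16.0 | 94.1% | 7.80 | 86 |

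The table isolates the effect of visit 1 volume. It leaves out what centre and AHI stratum would explain or cost in df.

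**Step 3: how large could r be?** For a change score, r depends on the correlation ρ between the two volumes and on the ratio k of the visit 6 SD to the visit 1 SD:

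r = (ρk − 1) / √(1 + k² − 2ρk)

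With ρ = 0.8 (assumed):

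- k = 0.7: (0.56 − 1)/√0.37 = −0.72
- k = 1: (0.80 − 1)/√0.40 = −0.32
- k = 1.2: (0.96 − 1)/√0.52 = −0.06

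So the same strong correlation between visits can go with a large gain or almost none.

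**Step 4: chance imbalance.** A one-standard-error imbalance in visit 1 volume moves the unadjusted estimate by |r| × 20 × √(2/67) = |r| × 3.46 cm³. That is 1.0, 1.7 and 2.1 cm³ at |r| = 0.3, 0.5 and 0.6. The factor 3.46 cm³ is itself the standard error of the unadjusted difference, so this movement is part of the uncertainty that the t test already reports.

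**The case against.** The strongest reply is that this is covariate detail for the statistical analysis plan, which the article mentions and which is not shown. The words "analysis of covariance model with adjustments at least for the stratification variables used at randomization" set a minimum, and nothing bars baseline volume. The optional wording in the next paragraph concerns outcomes taken at study end, which would not otherwise account for baseline; the primary outcome is already a change from visit 1. That sentence therefore need not signal any intent to keep baseline volume out.

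Much of this stands. A reader might infer that the plan excludes visit 1 volume. The text does not say so: the volume is not required, which is different. A reader might also take it to be the strongest predictor available, but the document reports no correlation, and a good predictor of final volume can be a weak predictor of change (step 3).

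The argument from starting size is also partial. A small lesion cannot shrink much but it can grow, and if the spread of change rises with lesion size, a linear covariate does not cure the unequal variance. The article provides a non-parametric fallback for failed model conditions. However, the Van Elteren test is a stratified rank test, and on centre and AHI strata it would not adjust for a continuous baseline volume.

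The reply does not remove the point. The article does state the minimum covariate set for its primary model, and a better minimum is available at almost no cost.

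**Conclusion.** The point holds as a free improvement, not as an error. The required adjustment covers centre and AHI stratum only, and visit 1 infarct volume is neither required nor prespecified for the primary model.

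The size is conditional on r. At |r| = 0.2 the gain is slight (power about 82%, detectable difference about 9.6 cm³). At 0.3 it is modest (84%, 9.3 cm³), and at 0.5 substantial (90%, 8.45 cm³). Near 0 it is negligible. These figures assume an SD of change of 20 cm³, 67 analysed patients per arm and a linear relation.

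Two stronger conclusions might be inferred, and neither is supported. First, the comparison is not biased, because randomisation protects the unadjusted estimate; a shift of about 2 cm³ from chance imbalance needs |r| near 0.6 and already lies within the unadjusted standard error of about 3.5 cm³. Second, the power statement is not wrong: it was derived without baseline adjustment and it reproduces, so any gain would come on top of it.

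**What to change.** State that the primary ANCOVA of volume change includes treatment, centre, AHI stratum and visit 1 DWI infarct volume, with baseline volume on the same scale as the outcome. If the statistical analysis plan already says this, a statement to that effect is enough.

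The cost is one sentence and one degree of freedom. No new data are needed: the volume is measured before ASV as part of the primary endpoint, and the day 1 MRI is already used to confirm lesion diameter before randomisation. The sample size statement can stay as it is.
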